### Strategies to improve adherence to interventions {11c}

During hospital stay, each IMP will be administered by nursing staff, so compliance issues are not relevant.

After discharge from the hospital, a patient diary will be used. In parallel, the patient will be asked to bring all the original drug packages at the follow-up visits, to check for the number of taken and remaining pills. The medical staff will record any incompliance on the database.

### Relevant concomitant care permitted or prohibited during the trial {11d}

Participation to other studies is not allowed.

Elective surgical procedures are allowed only after temporary discontinuation of mTOR inhibitors.

### Provisions for post-trial care {30}

During their participation in the clinical trial, the patients will be insured as defined by legal requirements. The investigator of the clinical trial will receive a copy of the insurance conditions of the “patients’ insurance.” The sponsor is providing insurance in order to indemnify (legal and financial coverage) the investigator/center against claims arising from the study, except for claims that arise from malpractice and/or negligence. The compensation of the subject in the event of study-related injuries will comply with the applicable regulations.

Patients’ insurance will be stipulated with Zürich Versicherungs AG as part of the contract with MedUniWien (Polizzennummer: 07229622-2)

Details on the existing patients’ insurance are given in the patient information sheet.

### Outcomes {12}

#### Primary endpoint

eGFR calculated by the CKD-EPI formula at 24 months after transplantation

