**Methods:**

A randomized prospective clinical trial has been set up to answer the research hypothesis. One hundred ten patients will be randomized in two groups. Treatment group will receive the new maintenance immunosuppression protocol based on low-dose tacrolimus and low-dose everolimus and the control group will receive our standard immunosuppression protocol. Both groups will receive alemtuzumab induction therapy. The primary endpoint of the study is to analyze the effect of the new low-dose immunosuppression protocol on kidney function in terms of eGFR change. The study will have a duration of 24 months from the time of randomization. Immunomodulatory status of the patients will be assessed with flow cytometry and gene expression analysis.

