## Objectives {7}

According to our preliminary experience, the use of alemtuzumab induction and the consequent reduction of CNI is associated with an improvement of glomerular filtration rate. However, long-term kidney function is still impaired by the steady cumulative kidney damage driven by tacrolimus. In parallel, despite excellent freedom from acute rejection, chronic rejection rate is still high with approximately 25% of patients at 5 years [43]. This trial proposes a new immunosuppression protocol based on the early administration of low-dose everolimus in the attempt of preventing CNI-driven kidney damage and stimulating allograft tolerance. The addition of de novo everolimus early after transplantation, in fact, has two potential advantages: (1) it allows a significant reduction of nephrotoxic tacrolimus and (2) together with alemtuzumab it could have a permissive influence on regulatory cells development with reduction of chronic rejection rate.

Our primary objective is to analyze the effect of the proposed low-dose immunosuppression protocol on kidney function. As secondary objectives we intend to assess the difference between the investigational and the control immunosuppression protocol in terms of freedom from ACR, AMR, and CLAD, overall survival, occurrence of de novo donor-specific antibodies (DSA), occurrence of CMV infections, and occurrence of other comorbidities (e.g., hypertension, dyslipidemia, diabetes, tremor). As experimental objectives, immunomodulatory cell subsets will be characterized overtime and gene expression will be profiled in both groups, to gain insight into the potential immunomodulatory mechanisms of the proposed low-dose immunosuppression.

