### Sample size {14}

#### 110 participants, 55 per group

Sample size calculations are based on available retrospective data of 231 patients treated with our standard protocol (control group). eGFR data are shown for all these patients (left panel) and after 7 outliers were removed who had initial values of eGFR > 220 (right panel).

Our modeling approach assumes that for each patient eGFR strongly drops over the first 6 months and from then on only mildly decreases for the next 6 months. After 12 months, eGFR has stabilized and does not change for each patient till the end of the study after 24 months. The value obtained after 12 months for each patient is modeled as a random intercept. The decrease over the first 6 months differs significantly between patients and is therefore modeled by an additional random effect. To model the longitudinal data, we applied thus the following mixed effects model:
$$ {Y}_{ij}={\beta}_j+{\gamma}_{0i}+{\gamma}_{1i}{c}_j+{\epsilon}_{ij} $$

Index *i* refers to the *i*th individual and index *j* ∈ {1, …, 5} corresponds to the time points 0, 3, 6, 12, and 24 months, respectively. The fixed effects *β*_*j*_ model the average of eGFR at a given time point. $$ {\gamma}_{0i}\sim N\left(0,{\sigma}_o^2\right) $$ is the random intercept and $$ {\gamma}_{1i}\sim N\left(0,{\sigma}_o^2\right) $$ is the random slope for each individual. The (non-linear) random slope is defined by the vector *c* = [1, 0.5, 0.1, 0, 0] which allows each individual to have a different amount of decrease of eGFR within the first 6 months. Consequently, this model allows for more variance (and less correlation between time points) at the beginning of the trial. The final term $$ {\epsilon}_{ij}\sim N\left(0,{\sigma}_{\epsilon}^2\right) $$ corresponds to the normally distributed error term. All random variables specified are assumed to be statistically independent.

Sample size calculations are based on an assumed effect size shown in the next graph. The blue line shows the estimated average behavior of GFR over time for the 224 patients after removing outliers. GFR stabilizes at 60 mL/min. The relevant treatment effect we want to detect is such that GFR stabilizes with the new immunosuppression protocol at 72 mL/min.

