To make best use of the longitudinal data, we are not only testing the difference in GFR between the two treatment groups at 24 months or at 12 months (which could be accomplished by a simple ANCOVA taking the baseline value for each individual as a covariate) but we actually want to compare the whole curves for the two treatments. To this end, we specify a time-dependent effect vector of the form *C*_*eff*_ = [0, 0.5, 0.9, 1, 1] where our main endpoint is the interaction between *C*_*eff*_ and the treatment group. The idea is that initially there is no difference between the two groups while the effect is increasing over the first 6 months and has reached its full amount after 12 months. The following plot presents power curves for this contrast for different group sample sizes and compares with the power of simple ANCOVA analysis of GFR after 12 months or 24 months, respectively.

In the first plot, we simulated exactly under the model described above (the same random effects and the same contrast *C*_*eff*_). The second plot is based on simulations where both the vector *c* defining the random effect as well as the vector *C*_*eff*_ specifying the treatment effect were slightly changed. In both cases, the mixed model (1) was extended to test the interaction between *C*_*eff*_ and treatment at a significance level *α* = 0.05. The power curves (based on 5000 simulation replicates) indicate that the model is fairly robust against slight perturbations of these two vectors and that 45 patients per group are sufficient to detect the specified effect with a power of 80% (we assumed for both groups a covariance structure as given by the preliminary data for the control group). Considering a potential dropout rate of 20% results in a sample size of 55 per group.

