#### Secondary endpoint analysis

Simple ANCOVA analysis for GFR after 12 months and after 24 months, respectively, will be performed.

Chi-square tests, Fisher exact tests, Mann-Whitney *U* tests, or ANOVA will be used to compare differences between the groups. Curves for survival will be generated with Kaplan-Meier method and compared by log-rank tests. A univariate and multivariable Cox regression will be performed to find predictors of survival and CLAD incidence.

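### The stated primary endpoint is eGFR at 24 months, but the quantity called the main endpoint and given the 80% power is a treatment contrast over all visits, which equals the 24-month difference only under an assumed effect shape

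*Protocol article*

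**What the plan says.** All references are to the protocol article.

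- **Outcomes {12}, Primary endpoint:** "eGFR calculated by the CKD-EPI formula at 24 months after transplantation". The Participant timeline {13} agrees: its eGFR outcome row is marked only at the end-of-study visit, 24 months after transplantation.
- **Sample size {14}:** the authors explain that "we actually want to compare the whole curves for the two treatments". They define C_eff = [0, 0.5, 0.9, 1, 1] at 0, 3, 6, 12 and 24 months, "where our main endpoint is the interaction between" C_eff and treatment group. The 80% power at 45 per group is for this contrast.
- **Sample size {14}, model assumption:** after 12 months, "eGFR has stabilized and does not change for each patient till the end of the study after 24 months".
- **Statistical methods {20a}, Primary endpoint analysis:** a mixed-model F-test fitted with lme. The term to be tested is not named there; that it is the C_eff interaction is inferred from the Sample size section.
- **Statistical methods {20a}, Secondary endpoint analysis:** "Simple ANCOVA analysis for GFR after 12 months and after 24 months, respectively, will be performed".

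**The concern.** One section names a single-visit endpoint. Another names a weighted contrast over the whole follow-up as the main endpoint and powers it. The only analysis that compares the arms directly at 24 months is secondary.

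A significant primary test would therefore not by itself show a difference in the stated primary endpoint, and a real difference confined to month 24 could be missed. In an open-label, single-centre trial, two candidate primary quantities also leave room to choose the headline once results are known. A report could take its claim from the Outcomes section and its p-value from the contrast in the Sample size section.

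**Working it through.** **Inputs from the Sample size section.** Visits at 0, 3, 6, 12, 24 months; C = C_eff = [0, 0.5, 0.9, 1, 1]; random-slope vector c = [1, 0.5, 0.1, 0, 0]; plateau effect 72 − 60 = 12 mL/min; α = 0.05; 80% power at 45 per group.

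**The plan's own figure.** The 80% cannot be reproduced. No standard deviations are printed and the power curves are in figures that are not shown. I use it as the calibration point instead.

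**Assumptions.** σ1/σ0 (random slope to random intercept) from 0.5 to 2, and σe/σ0 (residual to random intercept) from 0.3 to 1. The printed formulas give both random effects the same variance symbol; that case, ratio 1, lies inside the range. The article says only that the model was extended to test the interaction, so I ran it with and without a treatment main effect.

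**Method.** With free visit means, the covariance within a patient is V = σ0²J + σ1²cc′ + σe²I, where J is the all-ones matrix. The estimated coefficient is w′d, where d is the vector of between-arm differences by visit.

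- Without a treatment main effect: w = V⁻¹C / (C′V⁻¹C).
- With one: w is the C row of (X′V⁻¹X)⁻¹X′V⁻¹, with X = [C, 1].
- Calibration: SE = 12 / (1.960 + 0.842) = 4.28 at 45 per arm.
- Power ≈ Φ(w′d / 4.28 − 1.96); the opposite tail adds at most 0.2 percentage points.

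**Weights.** C and c take the same values at 12 and 24 months, so those visits always have equal weight: 0.35 to 0.41 without a main effect and 0.43 with one. Month 6 has 0.29.

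**Worked case.** σ1/σ0 = 1, σe/σ0 = 0.5, no main effect: w = (−0.454, −0.038, 0.294, 0.377, 0.377).

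- Planned profile (0, 6, 10.8, 12, 12): w′d = 12.0, power 80% by construction.
- Planned to month 12, zero at month 24: −0.038×6 + 0.294×10.8 + 0.377×12 = 7.5. Power = Φ(7.47/4.28 − 1.96) = Φ(−0.21) ≈ 42%.
- 12 mL/min at month 24 only: 0.377×12 = 4.5. Power ≈ 18%.

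**Whole range, both model forms**

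| True between-arm difference at 3, 6, 12, 24 months | Primary estimate (mL/min) | Chance of significance, 45 per arm | 55 per arm |
|---|---|---|---|
| 6, 10.8, 12, 12 (as planned) | 12.0 | 80% (calibrated) | 87% |
| 6, 10.8, 12, 0 | 6.9–7.8 | 36–44% | 43–52% |
| 6, 10.8, 12, −6 | 4.3–5.7 | 17–26% | 20–31% |
| 0, 0, 0, 12 | 4.2–5.1 | 17–22% | 19–26% |
| 6, 10.8, 12, 18 | 14.1–14.6 | 91–93% | 95–96% |

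**Power of a 24-month ANCOVA.** Conditional variance V₅₅ − V₅₁²/V₁₁, 12 mL/min, 45 per arm, same calibration: 59 to 77% if the contrast model has no treatment main effect, about 80 to 100% if it has one.

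**The case against.** The strongest defence is that the contrast was chosen openly, to use the longitudinal data, and that under the planned shape its coefficient is the 24-month difference. With no effect at any visit, nothing here shows an inflated type I error. The 24-month ANCOVA is prespecified, so a direct estimate will exist. The authors also simulated under changed vectors. All of this stands. However, those vectors were only slightly changed, which does not cover an effect that fades or emerges in the second year.

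Four stronger readings are tempting, and the documents do not support them.

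- **That the 24-month endpoint has less than 80% power.** The direction turns on whether a treatment main effect is fitted, which the article does not fix, and its ANCOVA power curves are not shown.
- **That Table 2 contradicts the plateau.** The plateau that matters is in the between-arm difference; changes common to both arms go into the free visit means. MMF starts in both arms. At range midpoints the tacrolimus gap is 7 − 3.5 = 3.5 ng/ml before month 12 and 6 − 2.5 = 3.5 after.
- **That the rationale predicts a fading effect.** The Objectives say that "long-term kidney function is still impaired by the steady cumulative kidney damage driven by tacrolimus". This concerns the long term and, if it acted within 24 months, would suggest a widening gap, in which case the contrast understates the month-24 benefit (last table row). No passage predicts that the effect will vanish; that profile is a stress test.
- **That the abstract adds a third endpoint.** Its phrase "kidney function in terms of eGFR change" is shorthand for the objective and is not defined separately.

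**Conclusion.** The mismatch is real and needs no modelling to see: the article gives two different primary quantities, and the 80% power belongs to the C_eff contrast, not to the endpoint in the Outcomes section. They are the same quantity only if the between-arm difference follows C_eff with a plateau from 12 to 24 months.

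If it does not, the gap is material. At 45 per arm there is a 36 to 44% chance of a significant primary test with no month-24 difference, and 17 to 22% power when the full 12 mL/min is present only at month 24. These figures rest on variance components scaled to the stated 80% and on the assumed ratio ranges, and the conclusion holds across that grid in both model forms. It also rests on the inference that the F-test addresses the C_eff interaction. The power for the 24-month endpoint is simply not stated.

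**What to change.** Make endpoint, test and power refer to one quantity, and name the tested term in the Primary endpoint analysis section. There are two ways.

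- **(a) Keep the powered contrast.** Reword the primary endpoint in Outcomes and the eGFR row of the Participant timeline as the C_eff-weighted eGFR difference. Report the month-24 contrast with its 95% CI, from the same mixed model, as the first key secondary result. Base no 24-month claim on the primary p-value.
- **(b) Keep eGFR at 24 months.** Test the treatment-by-month-24 contrast in a mixed model with visit as a categorical factor, make the C_eff contrast supportive, and state the power for the month-24 contrast.

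Either way, state whether the model contains a treatment main effect. The cost is wording and order of analysis, with no new data. Option (b) also needs a fresh power calculation from the retrospective covariance estimates, which the authors used for the existing one; the result could be above or below 80%. The choice should be documented by amendment before eGFR is compared between the arms.

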#### Secondary endpoints

Incidence of acute cellular rejectionIncidence of lymphocytic bronchiolitisIncidence of antibody-mediated rejectionIncidence of chronic lung allograft dysfunctionIncidence of dnDSASurvival

### Participant timeline {13}

**Table Tabb:** 

		Study period					
		Screening	Randomization	Follow-up			EOS visit
Timepoint**		***Evaluation for Tx***	***30 to 60 POD***	***3 months after Tx***	***6 months after Tx***	***12 months after Tx***	***24 months after Tx***
**Screening:**							
**Eligibility screen**		X					
**Informed consent**		X					
**Randomization:**			*X*				
**Immunosuppression:**							
**Control group:**	**TAC + steroids**			X	X	X	
	**TAC + MMF + steroids**						X
**Treatment group:**	**Low-dose TAC + EVR + steroids**			X	X	X	
	**Low-dose TAC + EVR + MMF + steroids**						X
**Clinical assessments:**							
**Blood examinations**				X	X	X	X
**24 h urinalysis**				X	X	X	X
**Pulmonary function tests**				X	X	X	X
**ECG**				X	X	X	X
**Chest CT scan**						X	X
**Bronchoscopy with TBB and BAL**				X	X	X	X
**HLA-screening**				X	X	X	X
**Histological analysis of TBB**				X	X	X	X
**Microbiological analysis of BAL**				X	X	X	X
**Blood CMV count**				X	X	X	X
**Experimental assessments:**							
**FACS of T and B cells and DC**		X				X	X
**Gene expression analysis**		X				X	X
**OUTCOMES:**							
**eGFR at EOS**							X
**Freedom from ACR**				X	X	X	X
**Freedom from CLAD**							X
**Overall survival**				X	X	X	X
**Occurrence of de novo DSA**				X	X	X	X
**Occurrence of CMV infections**				X	X	X	X
**Occurrence of other comorbidities**				X	X	X	X

### Sample size {14}

#### 110 participants, 55 per group

Sample size calculations are based on available retrospective data of 231 patients treated with our standard protocol (control group). eGFR data are shown for all these patients (left panel) and after 7 outliers were removed who had initial values of eGFR > 220 (right panel).

Our modeling approach assumes that for each patient eGFR strongly drops over the first 6 months and from then on only mildly decreases for the next 6 months. After 12 months, eGFR has stabilized and does not change for each patient till the end of the study after 24 months. The value obtained after 12 months for each patient is modeled as a random intercept. The decrease over the first 6 months differs significantly between patients and is therefore modeled by an additional random effect. To model the longitudinal data, we applied thus the following mixed effects model:
$$ {Y}_{ij}={\beta}_j+{\gamma}_{0i}+{\gamma}_{1i}{c}_j+{\epsilon}_{ij} $$

Index *i* refers to the *i*th individual and index *j* ∈ {1, …, 5} corresponds to the time points 0, 3, 6, 12, and 24 months, respectively. The fixed effects *β*_*j*_ model the average of eGFR at a given time point. $$ {\gamma}_{0i}\sim N\left(0,{\sigma}_o^2\right) $$ is the random intercept and $$ {\gamma}_{1i}\sim N\left(0,{\sigma}_o^2\right) $$ is the random slope for each individual. The (non-linear) random slope is defined by the vector *c* = [1, 0.5, 0.1, 0, 0] which allows each individual to have a different amount of decrease of eGFR within the first 6 months. Consequently, this model allows for more variance (and less correlation between time points) at the beginning of the trial. The final term $$ {\epsilon}_{ij}\sim N\left(0,{\sigma}_{\epsilon}^2\right) $$ corresponds to the normally distributed error term. All random variables specified are assumed to be statistically independent.

Sample size calculations are based on an assumed effect size shown in the next graph. The blue line shows the estimated average behavior of GFR over time for the 224 patients after removing outliers. GFR stabilizes at 60 mL/min. The relevant treatment effect we want to detect is such that GFR stabilizes with the new immunosuppression protocol at 72 mL/min.

To make best use of the longitudinal data, we are not only testing the difference in GFR between the two treatment groups at 24 months or at 12 months (which could be accomplished by a simple ANCOVA taking the baseline value for each individual as a covariate) but we actually want to compare the whole curves for the two treatments. To this end, we specify a time-dependent effect vector of the form *C*_*eff*_ = [0, 0.5, 0.9, 1, 1] where our main endpoint is the interaction between *C*_*eff*_ and the treatment group. The idea is that initially there is no difference between the two groups while the effect is increasing over the first 6 months and has reached its full amount after 12 months. The following plot presents power curves for this contrast for different group sample sizes and compares with the power of simple ANCOVA analysis of GFR after 12 months or 24 months, respectively.

In the first plot, we simulated exactly under the model described above (the same random effects and the same contrast *C*_*eff*_). The second plot is based on simulations where both the vector *c* defining the random effect as well as the vector *C*_*eff*_ specifying the treatment effect were slightly changed. In both cases, the mixed model (1) was extended to test the interaction between *C*_*eff*_ and treatment at a significance level *α* = 0.05. The power curves (based on 5000 simulation replicates) indicate that the model is fairly robust against slight perturbations of these two vectors and that 45 patients per group are sufficient to detect the specified effect with a power of 80% (we assumed for both groups a covariance structure as given by the preliminary data for the control group). Considering a potential dropout rate of 20% results in a sample size of 55 per group.

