## Statistical methods

### Statistical methods for primary and secondary outcomes {20a}

#### Primary endpoint analysis

An *F*-test for the primary endpoint using mixed model analysis will be performed using the function lme from the R package nlme.

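### Sample size {14}: 45 per group with 20% dropout gives 57 per group, not 55; the sentence is arithmetically wrong, with a small consequence for power

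*Protocol article*

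**What the plan says.** Sample size {14} is headed "110 participants, 55 per group". The planning effect is a control plateau where "GFR stabilizes at 60 mL/min" and a treatment plateau where "GFR stabilizes with the new immunosuppression protocol at 72 mL/min", a difference of 12 mL/min. The test is the treatment interaction with a time-dependent effect vector in a longitudinal mixed model, "at a significance level *α* = 0.05".

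From simulated power curves, the section concludes that "45 patients per group are sufficient to detect the specified effect with a power of 80" (per cent). The next sentence is the one at issue: "Considering a potential dropout rate of 20% results in a sample size of 55 per group". No inflation formula is given.

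Three other places bear on it:

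- Section {18b} repeats the 20%, citing preliminary data, and words it as an upper figure.
- Under Primary endpoint analysis: "An *F*-test for the primary endpoint using mixed model analysis will be performed".
- Section {20c} defines the modified intention-to-treat set as randomized patients with measurements at least at months 0 and 3.

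**The concern.** The sentence presents 55 as the result of two stated inputs, 45 evaluable patients and 20% dropout, and a reader can check it on the page. Neither the correct inflation nor the common shortcut returns 55. At the dropout rate the plan itself names, the number of completers falls below the number the plan says it needs. The figure of 55 per group is also the design figure in Trial design {8}, and the sentence that justifies it will probably be carried into the trial report. What is at stake is the accuracy of the sample-size justification and, to a lesser degree, the power that can be claimed at 20% dropout.

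**Working it through.** **Inputs from the article.** Evaluable patients per group n = 45; power 80%; α = 0.05, taken as two-sided because an F-test has no direction; difference 72 − 60 = 12 mL/min; dropout d = 0.20; enrolment N = 55 per group. Variance components are not given in numbers.

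**Step 1: try to reproduce 55.**

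- Correct inflation: n/(1 − d) = 45/0.80 = 56.25, rounded up to 57 per group, 114 in total.
- Common shortcut: n × (1 + d) = 45 × 1.20 = 54 per group.
- Neither gives 55. The stated figure is 57 − 55 = 2 per group, or 4 in total, below the correct one.

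**Step 2: what 55 supports.**

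- Completers at 20% loss: 55 × 0.80 = 44, one fewer than 45.
- Largest dropout that keeps 45: 1 − 45/55 = 10/55 = 18.2%. So 55 allows for 10 losses per group, and 20% is 11.
- For comparison, 57 × 0.80 = 45.6.

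**Step 3: power if dropouts contribute nothing.** The SD is not stated, so it is back-solved on the assumption that 45 per group gives exactly 80% in a two-sample comparison:

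- SD = 12/[√(2/45) × (1.960 + 0.842)] = 20.3 mL/min.
- Power at 44 = Φ(12/[20.3 × √(2/44)] − 1.960) = 79.1%. A noncentral t calculation also gives 79.1%.
- The loss is about 0.9 percentage points.

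**Step 4: power if dropouts contribute their visits.** The article's mixed model, with its own vectors for the random slope and the treatment effect, was evaluated by generalised least squares. The effect was scaled so that 45 complete patients per group give 80%. Each group had 44 completers and 11 dropouts. Five assumed sets of variance components were used: random-intercept SD 15 to 20, random-slope SD 15 to 30, residual SD 10 to 20.

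| When all 11 dropouts per group leave | Power |
|---|---|
| Before month 3 (no data used) | 79.1% in all five sets |
| After month 3 | 80.6% to 82.1% |
| After month 6 | 83.9% to 85.5% |
| After month 12 | 86.0% to 86.7% |

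**Step 5: precision of the starting figure.** With the 5000 replicates the article reports, the Monte Carlo standard error of a simulated power of 80% is √(0.8 × 0.2/5000) = 0.57 percentage points, or about ±1.1 points at 95%. The 0.9-point loss in Step 3 lies inside that.

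**The case against.** A reader might infer from Steps 1 to 3 that the trial misses its 80% power. The documents do not support that.

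- The 79.1% needs every dropout to contribute nothing. The planned analysis is longitudinal, and the modified intention-to-treat set keeps everyone with data at months 0 and 3. Only patients lost before month 3 drop out of it entirely.
- The 45 is read from simulated curves and is called sufficient, not the exact minimum. Power at 45 may be somewhat above 80%, and the curves are not available to check. The shortfall is also within simulation error.

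Two further inferences also fail. One is that there is no margin because 20% is the expected rate: section {18b} gives it as an upper figure, and section {14} calls it potential. The other is that the analysis sets remove still more patients. For the modified intention-to-treat set this counts early dropouts twice, since a patient lost before month 3 is already within the 20%. The per-protocol set does remove patients with major violations, but the stated power is not tied to that set.

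All of this limits the consequence and leaves the arithmetic as it was. The article does not itself argue that partial data make up the difference: section {14} inflates for dropout as lost patients, and section {20c} says no missing data are expected. The figures in Step 4 also rest on assumed variances. And a patient lost before month 24 has no value for the 24-month ANCOVA planned under Secondary endpoint analysis.

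**Conclusion.** The point holds as a minor arithmetic error. Inflating 45 for 20% dropout gives 57 per group. The stated 55 leaves 44 at that rate, and it retains 45 only up to 18.2% dropout.

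The effect on power is small: about 79% in the worst case, where no dropout contributes data, and probably 80% or more under the planned mixed model if dropouts leave after month 3. The first figure assumes exactly 80% power at 45 per group and a two-sample approximation with a back-solved SD. The second assumes the variance ranges listed in Step 4. The 45 itself could not be re-derived, because the article gives neither numeric variance components nor, in the text at hand, the power curves. A materially underpowered trial is not shown.

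**What to change.** Keep enrolment at 55 per group and correct the sentence in Sample size {14}, for example: *55 per group retains 45 evaluable patients with up to 18% dropout; at 20% dropout, 44 complete, and patients who leave after month 3 still contribute their data to the mixed model.*

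If a power figure is to accompany it, the sponsor should take it from its own simulation, rerun at 55 per group with dropout included and the assumed timing of dropout stated. The 79% above should not be copied in, since it comes from an approximation that discards all partial data.

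The cost is one sentence and, optionally, one rerun of existing simulation code. Design, recruitment and analysis do not change.
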